This study will be conducted as a cross-sectional comparative designed study. The primary aim of this study is to explore the metabolic risks and predictive factors associated with the hidden and apparent body fat profiles in 16 to 45 year old (post-menarcheal and premenopausal) NZ European, Māori and Pacific women. The primary outcomes are:Investigating the association between body composition profiles and markers of metabolic disease risk, including glucose, lipid and inflammatory marker profiles;Investigating dietary and physical activity patterns as predictive factors associated with body composition profiles;Investigating miRNA expression related to energy expenditure/storage as a predictive factor associated with body composition profiles.

The secondary outcomes are:Investigating associations/interactions between dietary and physical activity patterns and miRNA expression and how this may modulate the odds of having a specific body composition profile;Investigating taste perceptions as a predictive factor associated with the different body composition profiles;Investigating eating behaviour and habits as predictive factors associated with the different body composition profiles;Investigating nutrient intake as a predictive factor associated with the different body composition profiles.

We hypothesise that the “hidden fat” profile is associated with increased metabolic disease risk in NZ European, Māori, and Pacific women aged 16 to 45 years. We further hypothesise that for all women, dietary and physical activity patterns are predictors of a particular body composition profile by modulating miRNAs associated with energy expenditure/storage.

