The power for simple (one variable) logistic regression for the risk of having a “hidden fat” profile among people of normal BMI is equivalent to the power of the independent sample t-test (Vaeth and Skovlund 2004) for comparing the predictor variable mean between the hidden fat and normal fat profiles. With a sample size of 75 per group and equal variance within groups, 80% power is achieved for differences of 0.46 σ. For instance, preliminary data on total energy expenditure assessed using the Recent Physical Activity Questionnaire (RPAQ) estimates the standard deviation at 5.36 METs-h/day; if the true difference means between the body composition groups is 2.47 METs-h/day, the logistic regression coefficient will be significantly non-zero 80% of the time. Clinically, the difference of 2.47 METs-h/day equates to ~684 kJ/day (164 kcal/day)(Besson et al. 2010), which is considered within the target range of recommended energy expended each day in physical activity and/or exercise (Pescatello and American College of Sports Medicine 2014). We will consider logistic regression predictors from the dietary and activity pattern data, and separately for the miRNA measurements.

Based on our pilot study that showed a prevalence of 21% of NZ European women having a “hidden fat” profile, (Kruger et al. 2010b) a sample of ~1140 women will need to be screened (380 per ethnicity) to find ~75 women per profile group; or to explore new profiles. The study design and study procedures are illustrated in Figure 1.

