### Data handling and statistical analysis

Statistical analysis will be performed using IBM SPSS statistics (IBM Corporation, New York, USA). Descriptive statistics will be used to describe the baseline population using mean (standard deviation), median (25, 75 percentile) or frequencies summary statistics. Normality of distribution will be evaluated using the Kolmogorov-Smirnov test and examining normality plots. Non-normally distributed variables will be transformed into approximately normal distributions by logarithmic transformations and again tested for normality. Primary statistical analyses will involve ANOVA tests with post-hoc analysis and Bonferoni adjustments comparing body composition profile groups regarding metabolic disease risk markers and dietary and physical activity patterns and miRNA levels; multiple logistic regression analysis to determine odds ratios of having a “hidden body fat” profile based on dietary and physical activity patterns; and, separately, miRNA expression levels. Principal components analysis will be performed on the miRNA data using the PCP directive in GenStat to identify linear combinations of the miRNAs that account for most of the variation between individuals (Zacharewicz et al. 2014); and Pearson correlations to determine correlation coefficients between dietary and physical activity patterns and miRNA expression profiles. A p-value of <0.05 will be considered significant.

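### Diet/activity and miRNA are never in the same model for body-fat profile, so the stated interaction outcome and the miRNA-pathway hypothesis have no described analysis that can estimate them

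*Protocol article*

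**What the plan says.** **Objectives (Protocol article, Background).** The primary aim is to "explore the metabolic risks and predictive factors associated with the hidden and apparent body fat profiles". The first secondary outcome concerns associations and interactions "between dietary and physical activity patterns and miRNA expression and how this may modulate the odds of having a specific body composition profile". The second hypothesis, stated for all women, is that "dietary and physical activity patterns are predictors of a particular body composition profile by modulating miRNAs associated with energy expenditure/storage".

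**Analyses (Data handling and statistical analysis).** The regression is "multiple logistic regression analysis to determine odds ratios of having a “hidden body fat” profile". Diet/activity and miRNA do not enter it together, since the article describes the models as "based on dietary and physical activity patterns; and, separately, miRNA expression levels". Alongside it are three other analyses:
- ANOVA with Bonferroni-adjusted post-hoc tests across the profile groups, for metabolic markers, diet, activity and miRNA;
- principal components of the miRNA data;
- Pearson correlations between diet/activity and miRNA.

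**Sample size (Participants and sample size).** The separation is stated again: "We will consider logistic regression predictors from the dietary and activity pattern data, and separately for the miRNA measurements". The same section fixes the comparison, saying that the power of the one-variable logistic regression for the hidden-fat "profile among people of normal BMI is equivalent to the power of the independent sample t-test". This compares hidden with normal fat, at 75 women per group.

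**The concern.** An interaction on the odds of a profile is a property of a model that has profile as outcome and contains both predictors and their product. A claim that diet and activity work through miRNA needs at least the diet/activity association with profile once miRNA is taken into account. The article describes neither model and says twice that the two predictor sets are handled apart.

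If the plan is followed as written, a listed secondary outcome cannot be reported as worded. The through-miRNA part of the hypothesis would then rest on placing three separate results side by side. The aim also names predictive factors for apparent fat, yet the only regression outcome is hidden fat among women of normal BMI. One of the three designed groups therefore gets no odds ratio and no multivariable model.

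**Working it through.** **1. The plan's own logistic figure.** Inputs from Participants and sample size: 75 per group, difference 0.46 σ, power 80%, σ = 5.36 METs-h/day. Alpha 0.05 is stated; two-sided is assumed.
- Difference: 0.46 × 5.36 = 2.47 METs-h/day, as stated.
- Power by the two-sample t-test: noncentrality 0.46 × √(75/2) = 2.82 on 148 degrees of freedom gives 79.9%. The normal approximation gives 80.4%.

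The figure reproduces. It covers one predictor and one contrast (hidden versus normal fat). No power is stated for an interaction, a mediated effect or the odds of apparent fat.

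**2. Objectives against analyses.**

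| Stated question | Described analysis | What is left |
|---|---|---|
| Diet/activity associated with miRNA | Pearson correlation | Nothing; covered, without profile |
| Diet/activity associated with hidden fat | Logistic model, diet/activity only | miRNA-adjusted effect |
| miRNA associated with hidden fat | Logistic model, miRNA only | Diet/activity-adjusted effect |
| Diet/activity × miRNA on the odds of a profile | None | The whole question |
| Diet/activity acting on profile through miRNA | The separate links only | Any joint estimate |
| Predictors of apparent fat | Three-group ANOVA, no covariates named | Odds ratio, multivariable model |

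**3. Can the separate models pick up an interaction indirectly?** Assumed for illustration: independent standard-normal predictors x (diet/activity) and m (miRNA), 150 women, log odds = 0.6·x·m with no main effects. Over repeated simulated studies, the model with x alone and the model with m alone each rejected in about 4 to 5% of runs. That is the error rate under no effect, so in this scenario they carry no information on the interaction.

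**4. Could a joint model answer the question?** Assumed: log odds = 0.46·x + 0.46·m + b·x·m, two-sided 0.05. The 150 women are 75 + 75 in one ethnicity, and 3 × 150 = 450 with the three pooled.

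| Interaction log odds ratio b | 150 women | 450 women |
|---|---|---|
| 0.23 | about 20% | about 55% |
| 0.46 | about 65% | about 98% |

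These effects are not in the protocol. They show only that pooling over ethnicities makes the question partly answerable and that a single ethnicity mostly does not.

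**5. Is the change in odds ratio on adding miRNA a usable mediation estimate?** No. Take independent predictors, so that true mediation is zero, and a diet log odds ratio of 0.46 (odds ratio 1.58). Adding an miRNA predictor with log odds ratio 1.0 moved the simulated diet odds ratio from 1.47 to 1.59; with 1.5 it moved from 1.38 to 1.58. The odds ratio shifts although nothing is mediated, because odds ratios are non-collapsible.

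Sampling adds a second problem. Each profile is filled to 75 of 225, or 33%, whereas the pilot prevalence of hidden fat was 21%. A diet–miRNA association estimated in the pooled sample therefore reflects the sampling quotas as well as the population.

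**The case against.** The strongest reply is that the analysis section labels its ANOVA and logistic models as primary. Two separate logistic models match primary outcomes two and three, which are themselves listed separately. The interaction is secondary, and no model is named for the other secondary outcomes either, so the article may simply leave secondary models to a fuller document. On this view, fitting models separately for the primary outcomes does not rule out a later joint one.

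Part of this stands. The separate models suit the primary outcomes and should stay, and a fuller plan may hold more. But the through-miRNA hypothesis is not marked as secondary. The analysis section also already includes the correlations that serve the association half of the secondary outcome, so it is not confined to primary questions. What the article does state, twice, is separation.

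Three stronger readings are tempting, and the documents do not support them:
- **Apparent fat is not analysed.** It is: the ANOVA with post-hoc tests compares all three groups on diet, activity and miRNA, and no odds ratio for apparent fat is promised. The gap is a regression estimate.
- **The whole secondary outcome is unaddressed.** The correlations cover its association half, and each single link in the proposed pathway has an analysis. The product term and the joint estimate are missing.
- **The logistic model contrasts hidden fat with all other women, so a graded predictor would cancel out.** The analysis section names no comparison group, but the sample-size section sets it as normal fat within normal BMI. Cancellation would concern an analysis that is not planned.

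**Conclusion.** The point holds in a limited form. The described analyses cannot estimate a diet/activity-by-miRNA interaction on the odds of a profile, nor a miRNA-adjusted diet/activity effect, although the Background states an outcome and a hypothesis that need them. This follows from the text and rests on no numerical assumption. Apparent fat is compared in means but has no odds ratio; that is a lesser gap, measured against an exploratory aim.

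The size can only be illustrated. Under an assumed pure interaction the separate models reject at the nominal rate. Under assumed effects a product term has about 20 to 65% power in one ethnicity and about 55 to 98% pooled. The primary group comparisons and the stated logistic power are unaffected. The plan should be changed, but the defect does not undermine the study. Because the design is cross-sectional, any pathway result is associational whatever model is used.

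**What to change.** 1. Keep the separate logistic models for the primary outcomes, and name normal fat among normal-BMI women as the comparison in the analysis section too.
2. Add one joint model pooled over the three ethnicities, preferably multinomial with normal fat as reference, giving odds ratios for hidden and for apparent fat. Enter diet-pattern scores, activity, the leading miRNA component scores, age and ethnicity.
3. For the secondary outcome, add a small number of diet/activity × miRNA product terms, named before the data are analysed.
4. For the through-miRNA hypothesis, choose one of two routes. Either use a mediation method suited to a binary outcome that allows for sampling on profile, and report it as associational only; or reword the hypothesis as association. Do not report the raw change in odds ratio with and without miRNA as a mediation estimate.

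The cost is additional analysis work with no new data collection. Interaction estimates will be less precise than main effects, which is the reason to pool and to keep the product terms few. If the sponsor does not want this work, the alternative is to narrow the secondary outcome to associations and drop the pathway wording.

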### Ethics

Ethical approval was obtained from the Massey University Human Ethics Committee: (Southern A), Reference No.13/13.

## Discussion

An ethnic-specific focus aimed at weight maintenance has been recommended from previous NZ research (Metcalf et al. 2000). Overweight or obesity is a continual process and the effects of inappropriate lifestyle behaviour may often be missed when strictly assessing BMI as an indicator of over-nutrition. BMI provides only a crude measure of body fatness as it does not distinguish between weight associated with muscle or with fat. However, it appears to remain a useful estimate of the proportion of the population with increased risk of health conditions associated with obesity (World Health Organisation 2000), but may not be able to predict disease risk in those with normal BMI and varying adiposity.

Previous research has shown that a significant proportion of individuals with normal weight and subsequent normal BMI values had excessive body fat or “hidden” fat (Kruger et al. 2010a; De Lorenzo et al. 2006; Romero-Corral et al. 2010; Kruger et al. 2010b). This “hidden fat” profile may be linked with early inflammation and may be a key factor in the emerging epidemic of obesity and related disease risk (De Lorenzo et al. 2006; De Lorenzo et al. 2007). Pilot study data from our laboratory (Kruger et al. 2010a; Kruger et al. 2010b) revealed that in a free-living population (N = 116) of 18 to 44 year old NZ European women, 21.4% had a “hidden fat” profile and subsequent increased metabolic disease risk (identified through elevated fasting plasma leptin and insulin concentrations) and higher levels of sedentary lifestyle parameters.

Although a few studies have explored normal weight obesity (Marques-Vidal et al. 2008; Di Renzo et al. 2010; Romero-Corral et al. 2010; Karelis et al. 2004), not many studies have been specifically conducted to explore metabolic disease risk associated with high body fat (hidden or apparent), in premenopausal women. The typical central fat deposition following menopause and/or ageing may be absent in premenopausal women, despite the fact that women steadily gain weight from menarche to adulthood. It is therefore unclear where the hidden fat is situated in these women, especially if they are slender. It may be that excess fat in a lean person is hidden in the abdomen or elsewhere where it could pose health risks and cause metabolic dysregulation (Di Renzo et al. 2006; Huxley et al. 2010; Martinez et al. 2008; Cameron et al. 2009).

### Implications

The presence of normal weight obesity varies between 2 to 28% in women (Oliveros et al. 2014). The origins are unclear and may be due to environmental as well as genetic factors (Oliveros et al. 2014; Karelis et al. 2004). Common recommendations for appropriate dietary or lifestyle behaviours may be ineffective due to individual genetic variation. Dietary or physical activity behaviours may influence molecular mechanisms controlling metabolic activity and gene expression. MiRNAs can regulate the gene and protein networks that control substrate utilization and storage. Differences in behaviour that impact on miRNA expression need to be identified in different body composition profiles. Identifying these differences may assist in developing preventive recommendations (Arkadianos et al. 2007), and need to be specific to the locality and culture of the target population (Swinburn et al. 2004).

Because we do not know if and where slender women of different ethnicities with a normal BMI store hidden fat, it is important to identify this and its possible impact on women’s health. It is equally important to consider these issues in women with apparent fat and normal BF% to be able to make comparisons and explore tailored solutions. Our study will address a unique gap in health research knowledge by investigating multi-ethnic populations in NZ, identifying important physiological and behavioural predictors of metabolic disease risk. This research will assist in providing an important piece of the metabolic health versus body composition puzzle to fall into place and generate new pathways for treatment or early intervention.

## Abbreviations

ADP: Air displacement plethysmography
BF%: Body fat percentage
BIA: Bioelectrical impedance analysis
BMI: Body mass index
CVD: Cardiovascular disease
DDQ: Dietary diversity questionnaire
EDTA: Ethylene diamine tetra acetic acid
FFQ: Food frequency questionnaire
gLMS: General labelled magnitude scale
ISAK: International society for the advancement of kinanthropometry
miRNA: micro ribonucleic acid
METs: Metabolic equivalents
NZ: New Zealand
RPAQ: Recent Physical Activity Questionnaire
T2DM: Type two diabetes mellitus
TFEQ: Three factor eating questionnaire
